**C. OPERATIONAL DESIGN, UNINTENDED CONSEQUENECS & COST EFFECTIVENESS**

**Readiness for Food Based Intervention & Stakeholder Preferences on Design**

This section will aim at identifying key barriers and solutions for food supplementation to inform program design. It will be conducted at the time of baseline assessment. Specifically it will look into factors that may affect the overall operational research design, supply distribution chain and compliance of pregnant mothers and children.

*Acceptability:* Willingness for food supplementation program in the community will be explored across different stakeholders and need for advocacy/ communication in specific areas. Information will also be solicited to avoid contamination and cross over from Control to Intervention districts.

*Proposed Food Delivery Systems:* A number of aspects will be explored for proposed delivery systems and will include capacity, preferences and proposed measures for i) distribution outlets; minimization of supply breaks; adequacy of food storage; monitoring of food distribution; and minimization of pilferage and political capture. Also probed will be LHW presence on ground, and supporting factors that may be undertaken to enhance horizontal accountability of LHWs. The role of commercial sector in potential distribution and preparation of food will also be examined as well as the role of other district stakeholders in supporting the program in specific areas.

*End User Related Issues:* Client related issues will be examined in discussion with proposed users as well as local stakeholders. This will include product related factors such as demand for pre-prepared versus local foods; specific product preferences that may affect consumption. Decision making for use of prepared food in pregnancy and early childhood will also be probed in terms of cultural beliefs that may interfere with food use and identification of decision makers other than mothers who may influence use of food supplements. Barriers to IYCF will be explored including mothers’ occupation and implications for optimal feeding, cultural barriers, food preferences and availability of foods.

Extent of mothers’ interaction with LHWs and relationship with LHWs will be examined and preferred strategies for communication will be identified.

**Methods:** Mixed methods, largely qualitative but also supported by quantitative data will be used to assess readiness.

1. Household Survey:

Relevant indicators will be built into the baseline household survey (described above), on the following areas:

- Presence of LHW
- Willingness to be enrollment for pre-prepared food supplement

1. Key Informant Interviews:

Interviews will be conducted with district, union council level key informants to inform on willingness and acceptability of program; operational feasibility; proposed delivery and accountability systems; and measures to enhance uptake in the community. Interviews will be conducted with the following proposed stakeholders:

- Nutrition Focal Person, District Health Office, Thatta
- Local Focal Person, World Food Program, Thatta
- Local Focal Person, Merlin, Thatta
- Representative of Food Department, Thatta
- District Health Officer, Thatta
- District Coordinator, LHW Program, Thatta
- Union Council Nazim, (6 interviews - Intervention Union Councils)
- Lady Health Supervisors (6 interviews -Intervention Union Councils)
- Local CSOs, Thatta (3-4 interviews)
- Private sector traders
- Transporters
- Food producers
- Agricultural extension workers
- Teachers
- Local water committees

Key informants at district level will be purposefully selected following the above list, and further interviewees will be selected using snowballing approach. Stakeholders from Union Councils will be drawn from 6 randomly selected intervention Union Councils. A semi-structured questionnaire will be used to elicit open ended responses on identified areas. Transcripts will be uploaded in NVivo for analysis.

C. Focus Group Discussions (FGDs)

Focus Group Discussions will be conducted with participants from 6 villages in the proposed intervention area. 6 intervention Union Councils will be randomly selected and then one village will be randomly selected from each Union Council.

Focus Groups Discussions will be held with a number of grassroots level stakeholders to provide a triangulated perspective of locally perceived barriers and solutions. 12-15 participants will be recruited for each FGD. These are as follows:

- Village elders - 1 FGD
- Lady Health Workers – 1 FGD
- Pregnant & Lactating Mothers, Mother-in laws- 6 FGDs
- Spouses of Pregnant & Lactating Mothers – 6 FGDs

Data collectors (note takers and moderators) will be recruited from Thatta with command of local language. Male data collectors will conduct FGDs with male participants and female data collectors with female participants. FGDs will be conducted after taking informed consent, and at convenient time and place for participants. A topic guide with probes will be used for an informed discussion, the moderator will facilitate free flow of discussion while note takers take notes of important verbal and non-verbal communications and gestures. FGDs will be tape recorded after taking consent from the participants. Transcription will be carried out on real time basis and uploaded into N-Vivo for thematic coding and analysis.

**II.** **Period Assessments:**

Roll out and uptake of essential interventions will be assessed six monthly.

A. Logistics Management Assessment

Delivery systems will be assessed six monthly in terms of supplies stock outs, adequacy of food storage systems, and record maintenance. This will be done through Direct Observation Checklist, and a review of information systems and record, with assistance of a procurement specialist from AKU.

1. Food Consumption at Community Level. Rapid six monthly assessments will be done at the village level to assess the following:

- Presence of LHW
- Frequency of interaction with LHW
- Proportion enrolled into the program amongst eligible population
- Mother’s knowledge of delivery points for food supplementation
- Proportion who received food supplements amongst those enrolled
- Mother’s knowledge of appropriate usage of food supplementation
- Frequency of food supplementation usage by mother
- Willingness to continue food supplementation usage

1. Uptake of Essential Interventions by Households:

This will include:

1. Provision of BCC through lane meetings, women’s groups, household sessions
2. Antenatal care visits to skilled provider
3. Handwashing
4. Provision and use of folic acid
5. Provision and use of iron
6. Provision and use of Multiple Micronutrient supplementation
7. Provision and use of food supplements
8. Purchase and use of iodized salt
9. Knowledge and practices of delayed cord clamping
10. Neonatal vitamin K administration
11. Vitamin A supplementation
12. Essential immunizations
13. Kangaroo mother care for promotion of breastfeeding and care of preterm and SGA infants

Infant and child feeding practices will also be assessed through rapid appraisal on six monthly bases:

- Early initiation of breastfeeding (within one hour of birth)
- Exclusive breast feeding under 6 months
- Continued breastfeeding at 1 year
- Introduction of solid, semi-solid or soft foods
- Minimum dietary diversity
- Minimum meal frequency
- Minimum acceptable diet (apart from breast feeding)
- Consumption of iron-rich or iron-fortified foods

**III. End line Assessment of Operational Aspects & Consequences of Food Based Intervention**

Assessment of implementation gaps and of systemic consequences other than stunting will be done at end line, using multi-pronged assessment at community, union council and district level. These findings will be used to inform decision to scale up.

*Programmatic gaps between design and implementation*

This section will explore synergies and constraints to program implementation through Household Survey, Distribution System Assessment, Key Informant Interviews and FGDs. It will assess the outreach of the program to intended beneficiaries in terms of enrollment, distribution and actual usage of food supplements. It will further assess the efficiency of distribution systems, adequacy of monitoring of food distribution and vulnerability for political capture and leakages. It will also look into product acceptability at community and district level probing what might have been improved in terms of product related features (taste, consistency etc), storage at household level, preferred distribution outlets and cultural or other constraints to use of food supplements. A particular focus will be on connects between the food and preventive health measures at the programmatic level and at the village level, examining the horizontal accountability of LHWs, ease of communication and the depth of information provided on food delivery, food consumption and accompanying health messages. All aspects will be examined with the perspective of where can future improvements be made.

*Unintended consequences including positive and negative outcomes*

Unintended consequences of food supplementation programs have not been well explored in developing country settings. Western countries have highlighted obesity in food stamp programs but this is less applicable to impoverished settings such as Pakistan. Open ended exploration of both positive and negative outcomes will be done at district, UC and village level using Key Informant Interviews and FGDs. Areas explored will include potential for financial dependency on food supplements, crowing out of local foods by prepared supplements, demand overtaking supply, and other negative outcomes. Unintended benefits, not captured in stunting measurements, will also be explored such as better community linkage with LHW Program, enhancement of women’s agency and other positive outcomes.

**Methods:** Mixed methods will be used relying on quantitative assessments supported by exploratory qualitative data.

1. Household Survey:

Relevant indicators will be built into the baseline household survey questionnaire (discussed in separate section), on the following areas:

- Presence of LHW
- Frequency of interaction with LHW
- Proportion enrolled into the program amongst eligible population
- Mother’s knowledge of delivery points for food supplementation
- Proportion who received food supplements amongst those enrolled
- Mother’s knowledge of usage of food supplementation
- Frequency of food supplementation usage by mother
- Willingness to continue food supplementation usage
- Mother’s knowledge on IYCF
- IYCF practices
- Provision of BCC through lane meetings, women’s groups, household sessions
- Antenatal care visits to skilled provider
- Handwashing
- Provision and use of folic acid
- Provision and use of iron
- Provision and use of Multiple Micronutrient supplementation
- Provision and use of food supplements
- Purchase and use of iodized salt
- Knowledge and practices of delayed cord clamping
- Neonatal vitamin K administration
- Vitamin A supplementation
- Essential immunizations
- Kangaroo mother care for promotion of breastfeeding and care of preterm and SGA infants

B. Logistics Management Assessment

Delivery systems will be assessed six monthly in terms of supplies stock outs, adequacy of food storage systems, and record maintenance. This will be done through Direct Observation Checklist, and a review of information systems and record, with assistance of a procurement specialist from AKU.

1. Key Informant Interviews

Interviews will be conducted with district, union council level key informants to inform on willingness and acceptability of program; operational feasibility; proposed delivery and accountability systems; and measures to enhance uptake in the community. Interviews will be conducted with the following proposed stakeholders:

- Provincial Program Director, Nutrition, Government of Sindh
- Local Focal Person, World Food Program, Thatta
- Local Focal Person, Merlin, Thatta
- Representative of Food Department, Thatta
- District Health Officer, Thatta
- District Coordinator, LHW Program, Thatta
- Union Council Nazim, (12 interviews - Intervention Union Councils)
- Lady Health Supervisors (12 interviews -Intervention Union Councils)
- Local CSOs, Thatta (3-4 interviews)
- Any other

Key informants at district level will be purposefully selected following the above list, and further interviewees will be selected using snowballing approach. Stakeholders from Union Councils will be drawn from 12 randomly selected intervention Union Councils. A semi-structured questionnaire will be used to elicit open ended responses on identified areas. Transcripts will be uploaded in NVivo for analysis.

D. Focus Group Discussions (FGDs)

Focus Group Discussions will be conducted with participants from 12 villages in the intervention area. 12 intervention Union Councils will be randomly selected and then one village will be randomly selected from each Union Council. Focus Groups Discussions will be held with a number of grassroots level stakeholders to provide a triangulated perspective of locally perceived barriers and solutions. 12-15 participants will be recruited for each FGD. These are as follows:

- Village elders - 2 FGD
- Lady Health Workers – 2 FGD
- Pregnant & Lactating Mothers and mother in -laws- 12 FGDs
- Spouses of Pregnant & Lactating Mothers – 12 FGDs

Data collectors (note takers and moderators) will be recruited from Thatta with command of local language. Male data collectors will conduct FGDs with male participants and female data collectors with female participants. FGDs will be conducted after taking informed consent, and at convenient time and place for participants. A topic guide with probes will be used for an informed discussion, the moderator will facilitate free flow of discussion while note takers take notes of important verbal and non-verbal communications and gestures. FGDs will be tape recorded after taking consent from the participants. Transcription will be carried out on real time basis and uploaded into N-Vivo for thematic coding and analysis.

**Cost Effectiveness Analysis**

Cost effectiveness analysis will run through the full three years of the program. For our analysis we will have 2 arms whose cost effectiveness will be compared: Arm 1: food based and preventive health interventions; Arm 2: preventive health interventions only. The time frame for both will be three years of intervention

To be able to assess the cost effectiveness of the intervention and control arms current, we will compare interventions with a scenario of doing nothing to improve child health. Incremental cost effectiveness ratios will be computed for each arm by calculating the incremental improvement over Do Nothing scenario.

A sensitivity analysis will be carried out to report results with or without 3% discounting for DALYs and using cost inputs for foreign prepared versus locally prepared supplements.

*Cost Calculation:* Unit costs for provision of food supplements and for delivery of preventive health measures will be developed based on programmatic records. A record of program inputs and costs will be maintained during the length of the program and verified by an external accountant. 2013 as the base year will be kept as the base year with costs converted to 2013 purchasing power parity to remove the effect of inflation. All costs will be summarized in US dollars and future costs discounted at 3%.

*Effect Calculation*: Percent reduction in stunting will be taken as the effect outcome. Efficacy will be obtained through Before After household survey. Changes in linear growth will also be calculated.

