**Preamble**

Widespread food insecurity and malnutrition are largely the main impairing factors for human capital development in the Pakistan. Rates of chronic malnutrition are very high, and acute malnutrition is critical: 44% of children under five are stunted and nationwide global acute malnutrition (GAM) rates amongst children under five exceed the WHO critical threshold of 15%. Nutritional status trends also show a deteriorating situation since 1994, when stunting rates were at 36%.

Recurrent crises in recent years such as the devastating 2010 floods have contributed to a sharp decline in food security, despite sufficient national food production of staples. Currently, 104 million people, or 58% of the population, are estimated to be food insecure. National nutrition survey 2011 shows that stunting under-five children is significantly higher in food insecure households [1].

Children under two are consuming less than half of their daily energy requirements (560 kcal) and lower than recommended levels of micronutrients (one-third of RNI for Iron and one-half for Zinc). Overall, less than 4% of children were receiving an acceptable, diverse diet [2]. High under-five child morbidity is also noted- 22% of the children had ARI on the day of the survey and 12% had diarrhea, while another 22% had diarrhea in the previous two weeks [1].

There is not only the overall issue of appropriate child care practices but also of food diversity and nutrient quality. The widely spread food insecurity is attributable mainly to lack of access. Nearly 27% of the population is living in extreme poverty while nearly half are estimated to be suffering from multi-dimensional poverty and intensity of deprivations.

Food security and nutrition situation in Sindh province is even more dramatic. According to the National Nutrition Survey, 2011, GAM prevalence exceeds 18% while anemia levels amongst children under five reached the alarming level of 72.5% [1]. With this high level of poverty and food insecurity, a food based approach to prevent stunting, together with non- food based approaches is needed.

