**Methodology and Study Design:**

The effectiveness of the project will be measured in terms of the impact of the proposed interventions on the stunting and micronutrient deficiency prevalences in the target group (children and mothers). Given the conditions of project implementation, a quasi-experimental “double difference” design would be appropriate to assess the impact of the intervention. We propose to compare the intervention and non-intervention (control) groups before (first difference) and after the intervention (second difference).

Then, the operational implementation of the research comprises a baseline and end line surveys. In addition, a nested cluster randomized controlled trial will be implemented to track the evolution of key variables related to the quality of intervention delivery and intermediate nutrition outcomes. The control clusters will receive routine public and private health services available in the area. The overall research design is shown in Figure 1.

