**Figure 1: Overall research design**

[figure not shown]

To ensure the robustness of this program a baseline and endline surveyswith a nested cluster randomized control trial to evaluate the programme in terms of nutrition and other core indicators is required. Therefore Division of Women & Child Health Aga Khan University proposes two separate cross sectional surveys which will be conducted in the target union councils of District Thatta-Sajawal to address the objectives of impact assessment of stunting prevention project. A baseline cross sectional survey will be conducted to provide benchmark indicators and frame work for the implementation of program. A structured questionnaire will be used to accomplish this information. At the end of the program an end line cross sectional survey will be conducted to assess the impact of the program, where the nutrition and other core indicators will be compared for pre and post intervention change.

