All household with pregnant women, lactating mothers and children under five years of age will be eligible for baseline survey. LHW khandan register will be used to identify and select the eligible subjects in intervention clusters where available. A unique identification number will be assign to both children and mothers at the time of recruitment for the baseline survey. Social mapping approach (meeting with community elders, mothers, dais, community midwife, community/social workers etc.) will be used to identify the eligible subjects in control clusters. A list of eligible subjects will be prepared based on social mapping method and households with eligible subjects will be randomly selected for baseline survey.

Similarly all households with pregnant women, lactating mothers and children under five years of age at the time of endline will be eligible for endline cross sectional survey. Eligible subjects will be randomly selected from both intervention and control areas to see the overall impact of intervention on target population.

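### The cost-effectiveness ratios rest on a before-after change set against a Do Nothing course that nobody surveys, which does not match the planned double difference

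*Protocol*

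**What the plan says.** The Methodology and Study Design section sets the impact estimator as a double difference: "We propose to compare the intervention and non-intervention (control) groups before (first difference) and after the intervention (second difference"). It adds that control clusters receive the routine public and private health services of the area.

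The text under Figure 1 describes the endline survey as the point "where the nutrition and other core indicators will be compared for pre and post intervention change". That sentence does not mention the control group. The section on sample size and design for the surveys does cover controls at endline: "Eligible subjects will be randomly selected from both intervention and control areas to see the overall impact of intervention on target population".

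The Cost Effectiveness Analysis section makes four statements that have to fit together:

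- Arms: "For our analysis we will have 2 arms whose cost effectiveness will be compared". Arm 1 is food plus preventive health; Arm 2 is preventive health only.
- Comparator: "Incremental cost effectiveness ratios will be computed for each arm by calculating the incremental improvement over Do Nothing scenario".
- Effect measure: "Percent reduction in stunting will be taken as the effect outcome".
- Source of the effect: "Efficacy will be obtained through Before After household survey".

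The only sensitivity analyses named there concern discounting and the price of the supplements.

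The Preamble reports 44% stunting in children under five and says: "Nutritional status trends also show a deteriorating situation since 1994, when stunting rates were at 36" per cent.

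**The concern.** A before-after change is the programme effect plus whatever stunting would have done anyway over the same three years. A double difference subtracts the control group's change and so removes the part of that trend that both groups share. The cost-effectiveness section does not call for that subtraction. It asks for one ratio per arm against doing nothing, and takes the effect from the before-after survey. Because no surveyed group stands for doing nothing, an analyst following the text would fall back on each arm's own baseline. That assumes stunting would have stayed flat.

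The document itself gives reason to doubt a flat course. The Preamble describes long-term worsening. The background sections also describe the 2010 floods and the 2011 rains, after which recovery could pull the other way.

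At stake is objective 6, cost-effectiveness. The Rationale section defines impact evaluation as measuring change attributable to the project and presents the evaluation as a basis for future investment. Arm 2 is the more exposed of the two. Its services are largely planned or already in place, so its true gain over three years may be small and its before-after change could be mostly trend.

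**Working it through.** The plan gives no figure for the cost-effectiveness effect, so there is none to reproduce. The check first takes the algebra, then an illustration of size, then the price of the alternative.

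**1. Where the trend goes.** Let *e1* and *e2* be the true reductions in stunting in Arms 1 and 2 against doing nothing, in percentage points. Let *t* be the rise that would have occurred anyway, taken as common to both arms.

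- Before-after reduction, Arm 1: *e1 − t*
- Before-after reduction, Arm 2: *e2 − t*
- Arm 1 minus Arm 2: *(e1 − t) − (e2 − t) = e1 − e2*

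The trend cancels in the contrast between arms but stays in each arm's own ratio. The protocol specifies the per-arm ratios.

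**2. Illustrative trend.** Inputs: 36% in 1994 and 44% later (Preamble). The Preamble attaches no year to the 44%; 2011, the year of the cited national survey, is an assumption.

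- (44 − 36) / 17 = 0.47 points a year
- 0.47 × 3 = about 1.4 points over three years

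**3. Size against the planned effect.** The survey sample-size section uses 49% and a 10% reduction without saying whether this is relative or absolute.

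| Reading of 10% | True effect | Before-after estimate with *t* = +1.4 | Share lost | Cost per point |
|---|---|---|---|---|
| Relative | 0.10 × 49 = 4.9 | 4.9 − 1.4 = 3.5 | 1.41 / 4.9 = 29% | × 4.9 / 3.49 = 1.40 |
| Absolute | 10 | 10 − 1.4 = 8.6 | 1.41 / 10 = 14% | × 10 / 8.59 = 1.16 |

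With the opposite sign, suppose stunting would have fallen by 1.5 to 3 points on its own (pure assumption):

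- The estimate of a true 4.9 becomes 4.9 + 1.5 = 6.4 to 4.9 + 3 = 7.9 points.
- The effect is overstated by 31% (6.4 / 4.9) to 61% (7.9 / 4.9).
- Cost per point is understated by 23% (4.9 / 6.4 = 0.77) to 38% (4.9 / 7.9 = 0.62).

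**4. Precision of the double difference.** Inputs: the stated 3200 per group, taken here as 3200 measured children per group in each survey round (assumption); design effect 1.5; 49% in three cells and 44.1% in the fourth; two-sided 5%.

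- SE = √[1.5 × (3 × 0.49 × 0.51 + 0.441 × 0.559) / 3200] = √(1.494 / 3200) = 2.16 points
- Power = Φ(4.9 / 2.16 − 1.96) = Φ(0.31) = about 62%
- With 3520 per group per round, power is about 66%; 80% would need about 4885.

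The 3200 itself does not follow from the stated inputs: two-sided 5%, 80% power and design effect 1.5 give 2439 per group for a relative 10% and 579 for an absolute 10 points. That is a separate matter; 3200 is used here only because it is the planned number.

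**The case against.** The best defence is that the before-after phrase only names the data source. The baseline and endline surveys are the vehicle of the double difference, they include control areas, and the cost-effectiveness section has two arms to be compared. If the arms' changes are subtracted, the result is the double difference and a common trend cancels.

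Much of this stands for the text under Figure 1, which follows directly on the double-difference paragraph and does not exclude controls. It is loose wording, not a rival estimator. The same goes for p1 and p2 in the sample-size section: they are inputs to a formula and do not define the analysis. The defence does not rescue the cost-effectiveness section. Subtracting the arms is never given as the effect there, and the specified ratios are per arm against Do Nothing, where the trend stays. Nor is this a detail left to an analysis plan, since the protocol itself fixes both the source and the comparator.

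Three stronger readings are tempting but unsupported:

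- A reader might infer that the impact evaluation as a whole is uncontrolled. It is not: the impact design is a double difference, and the primary outcome under Outcome Measures compares intervention with control.
- A reader might infer a known bias, for example an effect understated by 29%. The end year, the linear extrapolation of a national trend to two districts and the relative reading of 10% are all assumptions.
- A reader might infer that the double difference was chosen because a simple change cannot be attributed to the project. The Methodology section cites only the conditions of implementation; the attribution argument is in the Rationale section.

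**Conclusion.** The concern holds for the cost-effectiveness analysis. Followed as written, each arm's ratio absorbs the background trend, which is inconsistent with the double difference set out earlier in the same protocol. The wording under Figure 1 leans the same way and should be tidied.

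The sign and size of the bias cannot be determined from the documents. A trend of about 1.4 points, 29% of a 4.9-point effect or 14% of a 10-point effect, shows that it could matter and is not an estimate of it. The objective is secondary. Randomisation, data collection and the primary comparison are unaffected. This calls for correction before endline data are analysed, so that the choice cannot be influenced by the observed trend.

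**What to change.** In Cost Effectiveness Analysis:

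- Define the incremental ratio as Arm 1 against Arm 2. Its effect is the double-difference estimate of stunting from the baseline and endline surveys, with the cluster-based confidence interval carried into the ratio.
- State that Arm 2 is the surveyed control group, which this presumes.
- Either drop the per-arm ratios against Do Nothing, or label them as modelled, with an explicit assumed course of stunting under Do Nothing that is varied in the sensitivity analysis. Replacing only the before-after sentence would not be enough: a double difference gives one contrast between arms and no effect for either arm against Do Nothing.

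Under Figure 1, say that the indicators will be compared between intervention and control areas for change from baseline.

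Cost: no new data collection, since control areas are already sampled at endline. The comparator text has to change as well as the effect sentence. The interval will be wider than for a before-after change, with about 62% power for a 4.9-point effect on the assumptions above, and the plan should state that precision. The double difference removes only a trend common to both groups. Controls live in areas that Lady Health Workers do not cover, so a common trend is itself an assumption to be declared.
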